### Quality assurance for sites joining trial

The “learning curve” associated with TORS has been reported as a minimum of approximately 10 cases, with improvements in operating time noted after such learning is complete [14]. Importantly, such learning did not appear to affect the rates of positive margins. Prior to opening the study, in addition to local research ethics approval, each surgeon enrolling patients onto trial must have completed at least 10 previous TORS cases, and one such case will be proctored by one of the Principal Investigators ([name]). Each centre will be required to complete mock radiotherapy treatment plans, to ensure that such plans are designed in compliance with the protocol. The principal investigators will provide pertinent CT datasets. There will be three such mock plans: one node-negative radical case, one node-positive radical case, and one adjuvant case. Once these have been received and approved, the centre can be activated. Once the study is open, each centre may enroll and treat patients. For each patient enrolled on study and receiving radiation therapy, an electronic copy of the full radiation treatment plan must be sent to the principal investigators on or before the first day of treatment. Radiotherapy treatment can begin, but the plan will be reviewed within 5 business days to ensure there are no major deviations from the protocol.

### Statistics and sample size calculation

The study will employ a 1:1 randomization between Arm 1:Arm 2 (Figure 1) in a permutated block design. This sample size allows for one stratification factor at randomization, which will be HPV status: (positive vs. negative/indeterminate)

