#### Inclusion criteria

• Age 18 or older, providing informed consent

• ECOG performance status 0–2

• Histologically confirmed squamous cell carcinoma

• Primary tumor site in the oropharynx (includes tonsil, soft palate, base of tongue, walls of oropharynx)

• Tumor stage: T1 or T2, with likely negative resection margins at surgery

• Nodal stage: N0, N1 (≤ 3 cm), or N2 (between 1–3 cm, on either side of the neck), without extranodal extension on pre-randomization imaging.

• CBC/differential obtained within 4 weeks prior to randomization, with adequate bone marrow function, hepatic, and renal function, defined as: Hemoglobin > 80 g/L; Absolute neutrophil count >1.5 × 10^9^ /L, platelets > 100 × 10^9^/L; Bilirubin < 35 umol/L; AST or ALT < 3 × the upper limit of normal; serum creatinine < 130 umol/L or creatinine clearance ≥ 50 mL/min

• Patient assessed at head and neck multidisciplinary clinic (with assessment by radiation oncologist and surgeon) and presented at multidisciplinary tumor board prior to randomization.

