### Radiotherapy quality assurance

In order to ensure patient safety and effective treatment delivery, a robust quality assurance protocol is incorporated. The following requirements must be completed for each patient:

• Prior to treatment, each radiotherapy plan will be discussed at head and neck quality assurance (QA) rounds.

• All dose delivery for intensity-modulated plans (including arc-based treatments) will be verified with phantom measurements before treatment by physics staff.

• Cone-beam CT will be used to verify patient positioning immediately prior to treatment at minimum on a weekly basis, with orthogonal x-rays used on other days.

### Concurrent chemotherapy in arm 1

Patients with T1-T2N0 tumors will receive radiotherapy alone, and patients with T1-2 N1-2 tumors will receive radiotherapy with concurrent systemic therapy. Chemotherapy will consist of cisplatin 100 mg/m^2^ delivered every 3 weeks, in 3-week cycles. For patients who are deemed unfit for high dose cisplatin, the dose and/or schedule can be modified, or cetuximab or weekly carboplatin AUC 1.5 can be used, at the discretion of the medical oncologist.

### Salvage surgery in arm 1

Treatment response will be evaluated 8–10 weeks after completion of radiation therapy. For patients with residual nodes > 1 cm in size, a salvage neck dissection will be done. For patients with relapse or progressive disease at any time subsequent to radiation treatment, surgical salvage will be offered if feasible.

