### Adjuvant radiotherapy and chemotherapy

Adjuvant radiotherapy and chemotherapy will be delivered in accordance with National Comprehensive Cancer Network (NCCN) Clinical Guidelines [15]. Radiotherapy prescriptions and planning details are outlined above.

*Radiotherapy can be omitted* if there are no adverse pathological features (i.e. none of the following: extranodal extension, positive margins, pT3 or pT4 disease, nodal disease, or lymphovascular invasion).

*Adjuvant radiotherapy alone* is recommended for the following risk factors:

• Any node positive

• Lymphovascular invasion

• pT3 or pT4 tumor

• Close resection margins (<2 mm)

For patients with perineural invasion (PNI) alone and no other indications for radiotherapy, radiotherapy will be omitted [16].

*Adjuvant chemotherapy concurrent with radiotherapy* is required for patients with positive margins or extra-capsular extension. The chemotherapy will consist of cisplatin 100 mg/m^2^ delivered every 3 weeks, in 3-week cycles. For patients who are deemed unfit for such chemotherapy, the dose and/or schedule can be modified, or weekly carboplatin AUC 1.5 can be utilized, at the discretion of the medical oncologist.

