### Analysis plan

Patients will be analyzed in the groups to which they are assigned (intention-to-treat).

An independent-sample t-test will be used to compare QOL scores at 1-year on the MDADI. The percent of patients in each arm who experience a clinically significant QOL decline (10 points) will also be reported. Survival will be calculated from date of randomization using the Kaplan-Meier method with differences compared using the log-rank test. Pre-planned subgroup analysis will occur based on the stratification variable. A Cox multivariable regression analysis will be used to determine baseline factors predictive of survival. For the secondary endpoints involving QOL scales, linear mixed effects models will be used; for the MDADI, NDII and VHI-10, the total scores will be compared between the two arms, whereas for the EORTC scales, each of the subscales (e.g. pain, swallowing, etc.) will be compared between the two arms. The PNQ scores (A to E) will be converted to a numerical score (0 to 4, respectively), and the mean scores in each group will be compared with a t-test. In addition, the proportion of patients reporting severe neurological dysfunction (D or E) will be compared with the Chi-Squared Test, or Fisher's exact test, as appropriate.

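### The primary 1-year MDADI test is fixed as an unadjusted t-test, although baseline MDADI, HPV stratum and clinical nodal stage are known for every patient: precision is given up at no saving

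*Protocol article*

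**What the plan says.** - Randomization (Statistics and sample size calculation): 1:1 in permuted blocks, with one stratifier. "This sample size allows for one stratification factor at randomization, which will be HPV status", split as positive versus negative or indeterminate.
- Primary analysis (Analysis plan): "An independent-sample t-test will be used to compare QOL scores at 1-year on the MDADI". Sample size considerations names the same two-sided test. Neither section mentions a covariate.
- Other models (Analysis plan): "Pre-planned subgroup analysis will occur based on the stratification variable", and "A Cox multivariable regression analysis will be used to determine baseline factors predictive of survival". Mixed models are named for the secondary QOL endpoints, without a covariate list.
- Baseline data: MDADI is measured at baseline (Measurement of response), and QOL scoring is required within two weeks of randomization (Evaluation). p16 status is required for stratification (Human papillomavirus testing). Clinical nodal stage is an eligibility item (Inclusion criteria): "Nodal stage: N0, N1 (≤ 3 cm), or N2 (between 1–3 cm, on either side of the neck".
- Treatment rules: in Arm 1, "Patients with T1-T2N0 tumors will receive radiotherapy alone, and patients with T1-2 N1-2 tumors will receive radiotherapy with concurrent systemic therapy" (Concurrent chemotherapy in arm 1). In Arm 2, under Adjuvant radiotherapy and chemotherapy, "Any node positive" is one indication for adjuvant radiotherapy, beside lymphovascular invasion, pT3–4 and close margins. Adjuvant chemotherapy "is required for patients with positive margins or extra-capsular extension".

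**The concern.** The Background gives reason to expect swallowing-related outcome to follow treatment intensity. It reports that adding chemotherapy to radiotherapy raises long-term gastrostomy dependence from 1% to 13%, and that patients treated with TORS alone report better QOL than those who also had adjuvant therapy. Clinical nodal stage sets intensity in Arm 1 and is related to it in Arm 2, so it probably predicts 1-year MDADI. Baseline MDADI is a natural predictor of later MDADI. HPV status is balanced by the randomization, yet the stated test ignores it.

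An unadjusted test leaves whatever these variables explain in the error term. In a trial of 68 patients whose definitive comparison is this one endpoint, that precision is worth having, and the data to recover it are already required.

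**Working it through.** **1. The plan's own figure.** Inputs from Sample size considerations: difference 10, SD 12, two-sided alpha 0.05, power 90%, dropout 10%.

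n per arm = 2 × [12 × (1.960 + 1.282) / 10]² = 30.26. Dividing by 0.9 gives 33.6, rounded up to 34 per arm, 68 in total. The stated figure reproduces.

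**2. Unadjusted power.** 34 × 0.9 = 30.6 evaluable per arm. The noncentral t distribution with SD 12 gives 89.4%. The standard error of the difference is 12 × √(2/30.6) = 3.07 points.

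**3. Gain from nodal stage alone.** Let p be the N0 share and D the MDADI gap between N0 and N1–2. The article gives neither, so both are assumed: p from 0.2 to 0.4, D from 5 to 15, the same gap in each arm. Taking SD 12 as the total SD:

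share of variance explained R² = p(1−p)D² / 144; residual SD = 12 × √(1−R²).

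| D | R² (p = 0.2 to 0.4) | Residual SD | Power, 30.6 per arm |
|---|---|---|---|
| 5 | 3–4% | 11.8–11.7 | 90–91% |
| 10 | 11–17% | 11.3–11.0 | 93–94% |
| 15 | 25–38% | 10.4–9.5 | 96–98% |

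Example, p = 0.3 and D = 10: R² = 0.3 × 0.7 × 100 / 144 = 0.146; residual SD = 12 × √0.854 = 11.09; power 93.4%.

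**4. Check by simulation** (20,000 trials, 31 per arm, p = 0.3). With no treatment effect, the unadjusted test rejects in about 5% of trials. With a 10-point effect, power is 89.8% unadjusted against 93.2% adjusted for D = 10, and 89.8% against 90.2% for D = 5.

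**5. Chance imbalance is the same loss, seen another way.** At p = 0.3 and 30.6 per arm, the SD of the between-arm difference in N0 share is √(2 × 0.21 / 30.6) = 0.117. With D = 10 this moves the MDADI difference by 1.17 points (1 SD). The adjusted standard error is 11.09 × √(2/30.6) = 2.84, and √(2.84² + 1.17²) = 3.07, the unadjusted standard error in step 2. The imbalance is already inside that standard error and must not be counted again.

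**6. Baseline MDADI.** Its correlation with 1-year MDADI is not given. As an assumption, correlations of 0.3 and 0.5 on their own would give power of about 92% and 96% at 31 per arm.

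**The case against.** The strongest reply is that nothing here is wrong. The t-test is valid and unbiased under randomization, its type I error is about 5%, and 68 patients is correct for the stated inputs. If SD 12 is the total SD, the planned power already allows for nodal variation, and the gain rests on assumed values of p and D. At a 5-point gap it is negligible. All of this stands, and it makes the point an improvement rather than a defect.

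It can also be said that a condensed article leaves supportive adjusted analyses to the SAP. That is fair for supportive analyses. The primary test, however, is named in two sections of the article, so it is fixed here.

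A reader might infer more than the article supports:

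- *That nodal stage decides treatment intensity in both arms.* That is strict only in Arm 1. In Arm 2 adjuvant therapy follows pathology: nodes are one of several triggers for radiotherapy, and chemotherapy depends on margins and extra-capsular extension. Clinical stage is a proxy there.
- *That the trial is underpowered because SD 12 leaves out nodal variation.* In that case the total SD would be √(144 + p(1−p)D²), and unadjusted power would be 84–86% for D = 10 or 78–82% for D = 15. The article does not say what the SD covers, so this cannot be asserted.
- *That nodal stage should be a second stratifier.* Two binary factors leave on average 68/8 = 8.5 patients per stratum and arm, fewer in the small strata. The single stratifier is a reasoned choice, and HPV is prognostic for survival.
- *That the pooled difference hides two contrasts and needs an interaction test.* The stated objective compares strategies, so pooling is intended. With 30% N0 there are about 9.2 and 21.4 evaluable patients per arm by nodal stage. The interaction standard error is 12 × √(2/9.2 + 2/21.4) = 6.7 points, so 80% power needs about 2.8 × 6.7 = 19 points, nearly twice the target effect.

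**Conclusion.** The point holds as a free improvement. The stated primary analysis is sound but less precise than the required baseline data allow. Adjusting for clinical nodal stage alone adds about 1 percentage point of power if the N0 versus N1–2 gap is 5 MDADI points, about 4 if it is 10, and about 7 to 9 if it is 15. These figures assume 20–40% N0, a common gap in both arms, SD 12 as the total SD and 30.6 evaluable per arm. Baseline MDADI may add as much or more, depending on a correlation that the article does not give. The sentence allowing one stratification factor does not argue against adjustment, because a covariate creates no further randomization strata. No bias, alpha inflation or sample-size error follows.

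**What to change.** In Analysis plan, replace the t-test as primary analysis with a linear model of 1-year MDADI on arm, baseline MDADI, HPV stratum as randomized, and clinical nodal stage before treatment (N0 vs N1–2). Report the adjusted mean difference with its 95% confidence interval, and keep the unadjusted t-test as a sensitivity analysis. Use clinical, not pathologic, nodal stage: pathologic stage arises after randomization and only where surgery is done.

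Make the change before any unblinded data are seen, and preferably before the interim analysis, where QOL is shown by masked arm. The 10-point target and the 68 patients can stay, since the model estimates the same mean difference.

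The cost is a few lines of analysis text and three degrees of freedom. It needs no new data, visits or patients, and no change to the randomization.

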### Sample size considerations

This study will employ a randomized phase II screening design, to conduct a definitive QOL comparison as the primary endpoint, along with preliminary and non-definitive overall survival comparison between the two arms as a secondary endpoint [17]. The primary endpoint is the total score on all twenty items of the MDADI. It is generally believed that a 10-point difference in standardized QOL scores represents a clinically significant difference in QOL [18]. It is assumed that the QOL scores will be normally distributed with a standard deviation of 12. The study will use a two-sided, independent-sample t-test with an alpha level of 0.05 and power of 90%, and assume a dropout rate of 10%. There will be a 1:1 randomization between Arm 1 and Arm 2. In order to detect a 10-point improvement in QOL in the TORS arm (Arm 2), a total of 68 patients will be required (34 in each arm). Accrual targets are as follows: 10 patients in year 1, and 15–20 patients in years 2, 3, and 4.

### Analysis plan

Patients will be analyzed in the groups to which they are assigned (intention-to-treat).

An independent-sample t-test will be used to compare QOL scores at 1-year on the MDADI. The percent of patients in each arm who experience a clinically significant QOL decline (10 points) will also be reported. Survival will be calculated from date of randomization using the Kaplan-Meier method with differences compared using the log-rank test. Pre-planned subgroup analysis will occur based on the stratification variable. A Cox multivariable regression analysis will be used to determine baseline factors predictive of survival. For the secondary endpoints involving QOL scales, linear mixed effects models will be used; for the MDADI, NDII and VHI-10, the total scores will be compared between the two arms, whereas for the EORTC scales, each of the subscales (e.g. pain, swallowing, etc.) will be compared between the two arms. The PNQ scores (A to E) will be converted to a numerical score (0 to 4, respectively), and the mean scores in each group will be compared with a t-test. In addition, the proportion of patients reporting severe neurological dysfunction (D or E) will be compared with the Chi-Squared Test, or Fisher's exact test, as appropriate.

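### The primary 1-year MDADI comparison is fixed as an unadjusted single-visit t-test, which ignores the baseline and 6-month scores the trial collects and needs a stronger missing-data assumption than the mixed model already planned for the secondary QOL endpoints

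*Protocol article*

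**What the plan says.** The Analysis plan opens with "Patients will be analyzed in the groups to which they are assigned (intention-to-treat"), and its next statement sets the primary test: "An independent-sample t-test will be used to compare QOL scores at 1-year on the MDADI". No covariate or earlier score enters that test. Later the same section says "For the secondary endpoints involving QOL scales, linear mixed effects models will be used", and it names the MDADI total among the scores to be handled that way.

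Sample size considerations defines the outcome: "The primary endpoint is the total score on all twenty items of the MDADI". Scores are taken to be "normally distributed with a standard deviation of 12". The design is stated as "The study will use a two-sided, independent-sample t-test with an alpha level of 0.05 and power of 90"%, and the investigators "assume a dropout rate of 10"%. The target difference is 10 points in favour of TORS, giving 68 patients, 34 per arm.

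Measurement of response schedules the MDADI at baseline and every 6 months. A patient with no 1-year form will therefore usually have one or two earlier scores on the same instrument.

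**The concern.** Unless scores are imputed, a two-sample t-test at one visit includes only patients who have a score at that visit. The dropout inflation fits this reading, since it sizes the trial on about 61 of 68 patients supplying data. Two consequences follow.

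- **Bias.** The comparison is sound only if missing 1-year scores are unrelated to what those scores would have been, or if the loss shifts both arm means by the same amount. The arms receive different treatments with different early courses, and the outcome is swallowing-related QOL. Equal, uninformative loss is possible but should not be presumed.
- **Precision.** Baseline and 6-month scores predict the 1-year score to some degree. An unadjusted test makes no use of that.

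The article presents the QOL comparison as the trial's definitive result. As written, that result gets the method that uses less of the data, and the secondary QOL endpoints get the one that uses more.

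**Working it through.** **Inputs from the protocol article.** Difference 10, SD 12, two-sided alpha 0.05, power 90%, dropout 10%, 34 per arm (Sample size considerations). MDADI at baseline and 6-monthly (Measurement of response). 2-year overall survival of 82% to 90% in TORS series (Background).

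**Step 1: reproduce the sample size.** n per arm = 2 × [SD × (1.960 + 1.282) / difference]² = 2 × [12 × 3.242 / 10]² = 30.26. Allowing for dropout, 30.26 / 0.9 = 33.6, so 34 per arm and 68 in total. The plan's figure is reproduced.

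**Step 2: power on the patients expected to have a score.** 34 × 0.9 = 30.6 per arm. Exact t-test power is 89.4% there (90.3% by the normal approximation) and 92.3% if all 34 per arm were scored. The stated 90% power thus rests on completers.

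**Step 3: bias from unequal loss (assumed values).** Let d be the share missing in an arm and g the gap in points between its observed and missing patients. The full-arm mean equals the observed mean minus d × g, so the observed mean is too high by d × g. The bias in the difference is d₁g − d₂g. The documents give no loss by arm and no gap, so both are assumptions. With 15% versus 5% missing, the analysed numbers are 28.9 and 32.3, and the standard error is 12 × √(1/28.9 + 1/32.3) = 3.07.

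| Assumed gap (points) | Bias (points) | Type I error, no true difference | True 10-point benefit if RT loses more: seen as (power) | If TORS loses more: seen as |
|---|---|---|---|---|
| 10 | 1 | 6.2% | 9 (83%) | 11 |
| 20 | 2 | 10.0% | 8 (74%) | 12 |
| 30 | 3 | 16.4% | 7 (63%) | 13 |

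Type I error and power in this table use the normal approximation. With 10% missing in both arms and the same gap, the bias is zero, power is about 90% and type I error is 5%.

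**Step 4: how much of the allowance deaths could use.** Converting the cited 2-year survival at constant hazard (assumption), 1-year mortality is 1 − √0.90 = 5.1% to 1 − √0.82 = 9.4%. That is about half to nearly all of the 10% allowance. It is a rough range only, because those series differ from this trial's population.

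**Step 5: precision given up.** Adjusting for baseline with correlation r reduces the residual SD to 12 × √(1 − r²). The correlation is not in the documents and is assumed here.

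| r | Residual SD | Exact t-test power at 30.6 per arm |
|---|---|---|
| 0 (as planned) | 12.0 | 89.4% |
| 0.3 | 11.4 | 91.9% |
| 0.5 | 10.4 | 95.9% |

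**The case against.** **The intention-to-treat label.** A reader might infer that the plan claims intention-to-treat and then breaks it. The documents do not support that. The plan explains the term as analysis by assigned arm, and a t-test by assigned arm satisfies it. Nor does the plan say that only survivors who return the form are analysed. That is inferred from the test and the dropout inflation, and a t-test does not rule out imputation.

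**Rules may be elsewhere.** Handling of missing scores and deaths may be in the full protocol or SAP, which are not shown. Their absence from the article is therefore not a finding. The choice of primary test is different, because the article itself fixes it.

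**Who goes missing.** A reader might assume that the sickest patients drop out. No data in the article show this. Patients unable or unwilling to complete questionnaires are excluded, and visits are 3-monthly through year 2. The 15%/5% split is about 5 versus 2 patients of 34. Gaps of 20 to 30 points are 1.7 to 2.5 times the planned SD. The step 3 figures show sensitivity; they are not a forecast.

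**Two analyses of one instrument.** The 1-year score is primary and other time points are secondary, with a method named for each. That is not an inconsistency.

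**The remedy is imperfect.** A mixed model assumes missing at random, does not settle deaths, and gains little for the 12-month contrast from patients with only a baseline score. This stands, and it is why the fix includes a separate analysis for deaths.

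**Conclusion.** The point holds as a weakness in a stated method and should be changed. The primary test leaves out collected baseline and 6-month scores. It also relies on a stronger missing-data condition than a model the plan already uses for the same instrument.

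The precision loss is modest: 89% power against about 92–96%, if baseline and 1-year scores correlate at 0.3–0.5. Bias depends on the pattern of loss. It is nil when rate and gap are equal across arms, and 1 to 3 points in either direction under the assumed 15%/5% split. The larger of these matters against a 10-point target.

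The sample size is not in error, the intention-to-treat wording is not contradicted, and informative loss is a possibility rather than something the documents establish.

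**What to change.** Before any outcome data are seen, amend the Analysis plan so that:

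1. The primary estimate is the 12-month arm contrast from a linear mixed model of MDADI total score with baseline, 6- and 12-month scores, visit-by-arm terms and the HPV stratum. It includes every randomized patient with any score, in the assigned arm. The missing-at-random assumption is stated.
2. The 1-year t-test is kept as a supportive analysis.
3. One sensitivity analysis ranks deaths below all observed 1-year scores and compares the arms with a Wilcoxon test, since the mixed model does not settle deaths.

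The cost is a change of wording, slightly more analysis work and a model assumption to defend. The scores are already scheduled, so no new data or patients are needed.

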#### Evaluation

The following evaluations are required:

• History and physical examination by a radiation oncologist and head and neck surgeon within 8 weeks prior to randomization, including laryngopharyngoscopy.

• Staging within 12 weeks prior to randomization:

 ○ Contrast-enhanced CT of the head, neck, and chest

or

 ○ MRI of the head and neck with CT of the chest

• Histological confirmation of squamous cell carcinoma

• p16 or HPV tumor status

• CBC/differential, hepatic and renal function testing within 4 weeks of randomization

• Pregnancy test for women of child-bearing age within 2 weeks of randomization

• Dental evaluation within 6 weeks of randomization

• Assessment of dysphagia using CTC-AE version 4 within 2 weeks of randomization

• Completion of QOL scoring within 2 weeks of randomization

• Blood sample for mutational and copy number variation analysis (see section) within 4 weeks of randomization

• Signing of consent within 2 weeks of randomization

• Audiogram before initiation of treatment

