### Measurement of response

Survival outcomes: Overall survival will be measured as time from randomization until death from any cause, and progression-free survival as time to either progression or death, whichever occurs first.

QOL outcomes: The MDADI, EORTC scales, NDII, and VHI-10 will be measured at baseline and at 6-month intervals. PNQ will be completed at 1 year post-treatment.

Toxicity outcomes: CTC-AE toxicities will be recorded at every follow-up visit (3, 6, 9, 12, 15, 18, 21, 24, 30, 36, 42, 48, 54, and 60 months from the first date of treatment).

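### The primary t-test leaves out the baseline MDADI and the HPV stratum that the trial already records: it is valid, but gives up precision that an ANCOVA could recover at almost no cost

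*Protocol article*

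**What the plan says.** The primary test is named twice. Under *Sample size considerations*: "The study will use a two-sided, independent-sample t-test". Under *Analysis plan*: "An independent-sample t-test will be used to compare QOL scores at 1-year on the MDADI". Neither place mentions a covariate.

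Two pieces of pre-treatment information are available for every patient:

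- **Baseline MDADI.** *Measurement of response* states: "The MDADI, EORTC scales, NDII, and VHI-10 will be measured at baseline and at 6-month intervals". The required evaluations also list QOL scoring, and patients who cannot or will not fill in the questionnaires are excluded, so baseline scores should be nearly complete.
- **HPV status.** *Statistics and sample size calculation* states: "This sample size allows for one stratification factor at randomization, which will be HPV status".

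In *Analysis plan*, the stratification variable is used by name only for a subgroup analysis. Linear mixed models are assigned to the secondary QOL endpoints. The share of patients with a 10-point decline is also to be reported, which needs a baseline value. None of this changes the primary test.

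**The concern.** The protocol calls the 1-year QOL comparison definitive and sizes it with about 30 evaluable patients per arm. If baseline MDADI predicts 1-year MDADI, an analysis that omits it leaves explainable variation in the error term and widens the confidence interval. If HPV status predicts MDADI, stratified allocation balances it between arms while the t-test still counts it as noise, so the standard error is somewhat too large.

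What is at stake is precision. The sample size rests on one assumption about spread: "It is assumed that the QOL scores will be normally distributed with a standard deviation of 12". If the true SD is larger, adjustment recovers part of the lost power without recruiting anyone, in a trial that expects 10 patients in its first year and 15 to 20 in each of the next three. A full statistical analysis plan may exist, but because the article names the test, an adjusted primary analysis there would contradict it.

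**Working it through.** **Inputs from *Sample size considerations*:** difference 10, SD 12, two-sided alpha 0.05, power 90%, 10% dropout, 1:1 allocation, 68 patients. **Assumed, not in the protocol:** r from 0 to 0.5; an alternative SD of 16; the HPV prevalence and effect used in step 4.

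**1. The protocol's own figure.** Normal approximation, per arm: 2 × (12 × (1.960 + 1.2816) / 10)² = 30.26. Allowing for dropout: 30.26 / 0.9 = 33.6, rounded up to 34 per arm, 68 in all. The stated size is reproduced for the unadjusted t-test.

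**2. Power of the planned test.** Evaluable patients: 68 × 0.9 = 61.2, taken as 31 and 30. Standard error: 12 × √(1/31 + 1/30) = 3.07. Noncentrality: 10 / 3.07 = 3.25 on 59 degrees of freedom. Noncentral-t power is 89.3%, and the expected 95% interval half-width is 2.001 × 3.073 = 6.15 points. The shortfall from 90% comes from sizing with the normal approximation, not from omitting covariates.

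**3. ANCOVA.** Residual SD = SD × √(1 − r²), with 59 − 2 = 57 degrees of freedom after fitting baseline and HPV. HPV is given no effect here.

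| r (assumed) | Residual SD | Power, SD 12 | Half-width, SD 12 | Power, SD 16 |
|---|---|---|---|---|
| t-test | 12.00 | 89.3% | 6.15 | 67% |
| 0 | 12.00 | 89.2% | 6.15 | 67% |
| 0.2 | 11.76 | 90.4% | 6.03 | 69% |
| 0.3 | 11.45 | 91.8% | 5.87 | 71% |
| 0.5 | 10.39 | 95.8% | 5.33 | 79% |

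The residual SD column is for SD 12. At r=0 the cost is 89.26% − 89.22% = 0.04 percentage points.

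**4. HPV stratum alone.** Simulation with 30 per arm, HPV exactly balanced, overall within-arm SD held at about 12, 70% HPV-positive, 20,000 runs per setting.

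| HPV effect on MDADI (assumed) | Type I error, t-test | Power, t-test | Power, HPV-adjusted |
|---|---|---|---|
| 5 points | 4.3% | 88.9% | 89.6% |
| 10 points | 3.5% | 90.1% | 92.6% |

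If the stratifier is prognostic, the unadjusted test rejects a true null less often than the nominal 5%.

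**5. Chance baseline imbalance.** If baseline MDADI also has SD 12 (assumed), the baseline difference between arms has a standard error of 3.07 points. With equal SDs at the two times, about r times any imbalance carries into the 1-year difference: at r=0.5, a 6-point imbalance (about two standard errors) moves the unadjusted estimate by about 3 points.

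**The case against.** **The case for leaving the test alone.** The t-test is unbiased under randomization, the 68 patients were calculated for it, and it errs on the conservative side if HPV is prognostic. The gain hangs on a correlation that the protocol does not report and that may be low: patients enter with T1–T2 tumours, and the Background attributes dysphagia to treatment, so 1-year scores may depend mainly on what treatment did. At r=0.2 the gain is about one percentage point of power. No passage links HPV status to MDADI. If QOL scores differ substantially from the assumptions, the monitoring committee may also change the accrual target to maintain power.

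All of this stands, and it limits the point to efficiency. It does not give a reason to prefer the t-test, because the worst case for ANCOVA is a loss too small to matter. Changing accrual is discretionary and requires more patients; adjustment requires none.

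**Stronger readings that the protocol does not support.**

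- *That the t-test is biased or produces excess false positives.* It is not, and it does not (steps 4 and 5).
- *That a chance baseline imbalance passes in full into the result.* Only about r times the imbalance does, and over repeated randomizations the t-test's standard error already allows for it.
- *That baseline scores could be given after the arm is known.* A reader might infer this from "Completion of QOL scoring within 2 weeks of randomization". The same list uses that form of words for signing consent, and for blood counts, which *Inclusion criteria* places before randomization. Read with its neighbours, the phrase means before randomization.

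**Conclusion.** The point holds as a recommendation on efficiency. The definitive comparison uses the least efficient of the obvious analyses although the information for a better one is already collected. With the protocol's SD and difference, ANCOVA changes power from 89.3% to between 89.2% and 95.8% for r from 0 to 0.5, and shortens the interval half-width by up to 0.8 points (6.15 − 5.33). The gain is negligible at r of 0.2 or below, modest at 0.3 and worthwhile at 0.5. If the SD were 16, power would go from 67% to between 67% and 79% over the same range.

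That the primary test is unadjusted is certain. The size of the loss is not, because r and the alternative SD are assumptions. HPV should be in the model because it was used to stratify, but little gain should be expected from it unless its effect on MDADI is strong.

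**What to change.** In *Analysis plan*, define the primary test as the treatment coefficient, with its 95% confidence interval, from an ANCOVA of 1-year MDADI on arm, baseline MDADI and HPV stratum as used at randomization. Report the independent-sample t-test as a sensitivity analysis. Name the same primary model under *Sample size considerations*, and keep 68 patients; the t-test calculation can stay as the basis for that number.

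The change should be made before any outcome data are seen by arm. It takes a sentence in each of the two sections, no new data and two degrees of freedom, which is under 0.1 percentage point of power if baseline MDADI proves uninformative.
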